Finally, users of the iFightDepression® tool will be asked to complete the Patient Health Questionnaire (PHQ-9) which measures symptoms of depression at registration and six weeks later [74], in order to measure the impact of the tool on depressive symptoms. The PHQ-9 is a nine-item self-report questionnaire evaluating depressive symptoms, scored on a Likert scale of 0–3. Higher scores indicate a greater level of depressive symptoms.

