**Fig 2 pone.0352598.g002:**
[figure not shown]
Protocol Overview. Cross-country study protocol flowchart illustrating the main steps: region selection (control regions are shown within boxes with dashed borders), implementation of the 4-level intervention, evaluation components, and timeline (0–24 months; Mth = months).

Process evaluation: to comprehensively investigate the context-related implementation process of the intervention, including fidelity, reach, adoption, acceptability, and contextual facilitators and barriers across diverse European settings (Albania, Estonia, Greece, Ireland, and Spain).Outcome evaluation: To examine whether the expanded four-level intervention achieves its intended outcomes through a controlled, cross-country design. The evaluation will focus on clinical outcomes (e.g., reductions in suicidal behaviour and depressive symptoms) and non-clinical outcomes (e.g., improvements in wellbeing, self-reported mental health, and attitudes toward depression and help-seeking). Additionally, pre-post assessments without a control group will be included as well.Economic evaluation: to determine the cost-effectiveness of the intervention, expressed as the observed incremental cost per unit of outcome gained: cost per death by suicide avoided, per suicide attempt avoided and per percentage point improvement in selected clinical and subclinical outcomes derived from the population surveys conducted in each site.

The effectiveness of the expanded community-based 4-level intervention will be evaluated through a prospective controlled cross-country design across five European countries – Albania, Estonia, Greece, Ireland, and Spain. In each country, one intervention region and one comparable control region will be selected to allow for between-group comparisons. Primary clinical outcomes will be collected in both intervention and control regions to assess changes in depressive symptoms, suicidal behaviour, and wellbeing. Additionally, intermediate clinical and service-related outcomes will be collected in the intervention regions only to explore mechanisms of change and evaluate the broader system-level impact of the intervention.

The process evaluation will be conducted in both the intervention and control regions, using a mixed-methods approach that integrates both quantitative and qualitative data collection measures.

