Level 3: Community Facilitators. Training programs have been developed for community facilitators to enhance awareness, identification, and management of depression and suicidality across different professional sectors. The curriculum builds on the evidence-based EAAD training materials and was adapted through expert consultation and co-creation with national partners to ensure cultural and contextual relevance. The trainings aim to build confidence in recognising signs of distress, initiating supportive conversations, and referring individuals to appropriate services. Content and format were adapted to the specific professional roles and working environments of each group, ensuring relevance and feasibility. Targeted groups included teachers, pharmacists, counsellors, social workers, geriatric caregivers, journalists, police, and clergy, among others. The training lasts for 4–5 hours and is delivered by a mental health specialist, such as a psychiatrist or psychologist.

Level 4: Patients, High-Risk Groups, and Relatives. Psychoeducational materials have been developed to support both patients and their families in managing depression, as can be seen in Fig 2. These include a fact sheet on depression, an information leaflet for family members, and an Emergency Card with contact details for local emergency services and personal emergency contacts.

Furthermore, patients with mild to moderate depression may be referred to a guided online self-management tool for people with mild to moderate depression: the iFightDepression® tool [68,69]. The iFightDepression® tool is part of the EAAD materials and is designed for use by patients with mild to moderate depression, who are referred by trained primary care professionals, and who guide the patient’s use of this self-management tool, based on cognitive behavioural therapy techniques. Referral criteria include: (1) age ≥ 15 years (or younger if deemed appropriate), (2) mild to moderate depression (clinician-assessed), (3) access to internet and email, and (4) informed consent provided. Exclusion criteria are: age < 15 years (unless locally permitted), severe depression, acute suicidality, or current substance abuse.

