	Symptoms of depression in iFightDepression tool users	Online validated survey^g^ via iFightDepression tool (no control group)	At registering and 6 weeks later	Intervention regions only (not applicable to control regions)
Process	Reach of the intervention	Monitoring instrument and 4-level intervention tracker completed by research officers	During the 2-year implementation of the intervention	Intervention regions only (not applicable to control regions)
	Adoption, implementation, sustainability of the intervention	Interviews with research officers	After 24 months	Intervention regions only (not applicable to control regions)
	Adoption, implementation, sustainability of the intervention	Focus groups with stakeholders	After 24 months	Intervention regions only (not applicable to control regions)
	Satisfaction and acceptability of professionals (Level 1 and Level 3 trainings)	Online bespoke survey	Immediately after each training session	Intervention regions only (not applicable to control regions)
	Reach of the public campaign	Survey among general population (campaign awareness)	After 24 months	Intervention and control regions
	Reach of the iFightDepression tool	User data from iFightDepression tool and iFight4Wellbeing website	After 24 months	Intervention regions only (not applicable to control regions)
	Acceptability of the iFightDepression tool	Online survey among iFightDepression tool users	6 weeks after registration	Intervention regions only (not applicable to control regions)
	Acceptability of the iFightDepression tool	Online survey among iFightDepression tool guides	After 24 months	Intervention regions only (not applicable to control regions)
	Acceptability of the iFightDepression tool	Focus groups with guides of iFightDepression tool users	After 24 months	Intervention regions only (not applicable to control regions)
Cost	Direct costs of the intervention	Project cost tables, monitoring instrument, and exchanges with research officers	During the 2-year implementation of the intervention	Intervention regions only (not applicable to control regions)
	Costs of health care use and other resources used due to an (attempted) suicide	Estimates from literature, hospital data and expert opinion	Not applicable	Intervention and control regions
	Productivity losses due to an (attempted) suicide	Estimates from the literature, hospital data and expert opinion	Not applicable	Intervention and control regions

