### Process evaluation

The process evaluation will assess key aspects of implementation, such as reach, adoption, implementation, acceptability, and sustainability of the intervention. Multiple data sources will be used to capture these dimensions:

**Monitoring templates and trackers** to be completed by local research officers to document implementation activities (e.g., alliance functioning, awareness campaigns, training sessions, media engagement).**Semi-structured interviews** with local research officers to explore regional differences, facilitators, and barriers.**Satisfaction surveys for Level 1 and Level 3 trainees** to assess relevance, usability, and perceived impact of the trainings for professionals.**Satisfaction surveys for tool guides, and tool users** to assess relevance, usability, and perceived impact of the iFightDepression® tool.**Log data from the iFightDepression® tool** (e.g., number of registrations, repeat visits, total usage time) to evaluate engagement.**Focus group with stakeholders** in each country to evaluate the acceptability, implementation process, and sustainability of the intervention.

The design of the data collection instruments is grounded in three widely used implementation science frameworks. The Consolidated Framework for Implementation Research (CFIR) [20,78] guides the identification of barriers and facilitators across five domains (intervention characteristics, inner and outer settings, individual characteristics, and implementation processes) providing a nuanced understanding of contextual influences. The RE-AIM framework [21] informs the evaluation of key dimensions of implementation success, including reach, adoption, fidelity, and maintenance. Finally, the taxonomy of Proctor and colleagues [25] offers a structured set of implementation outcomes, such as acceptability, appropriateness, feasibility, and sustainability, that complement RE-AIM and enable a comprehensive assessment of how the intervention is integrated into practice. Together, these frameworks ensure that the process evaluation captures both contextual determinants and measurable indicators of implementation quality.

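### The six-week PHQ-9 change in iFightDepression users is said to measure the tool's impact, but it is an uncontrolled pre-post change and can only describe what happened to users

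*Protocol article*

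**What the plan says.** Under Outcome evaluation, users complete the PHQ-9 at registration and six weeks later, "in order to measure the impact of the tool on depressive symptoms". Table 3 places this indicator in the Outcome category, gives its timing as "At registering and 6 weeks later", and describes the source as an online survey "via iFightDepression tool (no control group"), in intervention regions only. Study aims and design says more generally that "pre-post assessments without a control group will be included as well", and that intermediate clinical and service-related outcomes are "collected in the intervention regions only to explore mechanisms of change and evaluate the broader system-level impact of the intervention".

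The description of Level 4 under Materials says how users arrive: "patients with mild to moderate depression may be referred to a guided online self-management tool". Severity is assessed by the clinician and no PHQ-9 threshold is given. Severe depression, acute suicidality and current substance abuse are excluded. Trained primary care professionals refer the patients and guide their use of the tool. Other treatment for depression is not among the exclusions.

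The Strengths and Limitations section acknowledges that the lack of randomisation and blinding limits causal inference. It offers matched control regions and baseline adjustment in response.

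**The concern.** The stated purpose is causal and the comparison is not. Measuring an impact requires some account of what PHQ-9 would have been at six weeks without the tool, and this component collects no data that supply one. Because patients enter while symptomatic, their scores would be expected to fall on average even if the tool did nothing. The article uses the term perceived impact for the satisfaction surveys under Process evaluation, so plain impact in the PHQ-9 sentence reads as actual effect.

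At stake is what may be concluded about Level 4. The wording allows a significant pre-post fall to be read as an effect of the tool. The sentence in Study aims and design that gives outcomes without a comparator the task of evaluating system-level impact allows the same step more widely. The primary outcome (hospitalisations for self-harm), the key secondary outcome (suicides) and the population surveys all have control regions and are not affected.

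**Working it through.** **No planned figure to reproduce.** The protocol gives no sample size, power, SD, correlation or target effect for this comparison. The check is therefore of the text, followed by an illustration on assumed values.

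**1. Text, side by side.**
- Purpose (Outcome evaluation): the impact of the tool.
- Comparator (Table 3; Study aims and design): none.
- Entry (Materials, Level 4): referral while depressed, judged by a clinician.
- Analysis (Statistical analysis): mixed models using all available data under missing at random. This deals with missing six-week scores. It does not replace an absent comparator.
- Limitation (Strengths and Limitations): concerns the comparison of regions, and its answer is the matched control regions. Tool users have no such controls.

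Nothing in these sections separates a tool effect from recovery, regression to the mean or other care.

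**2. Size of regression to the mean alone.** All inputs are assumptions: PHQ-9 bivariate normal in the population from which referrals come, mean μ = 6 to 10, SD σ = 5 to 6, six-week correlation r = 0.6 to 0.8, no tool effect and no recovery. The registration score is taken to lie in 5–19 or in 10–19 (from the lower value up to, but below, 20). Then

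expected fall = (1 − r) × (mean registration score of those entering − μ),

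where, with a = (lower − μ)/σ and b = (20 − μ)/σ, the bracket equals σ × [φ(a) − φ(b)] / [Φ(b) − Φ(a)].

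- Smallest case, entry 5–19, μ = 10, σ = 5, r = 0.8: a = −1, b = 2. Bracket = 5 × (0.2420 − 0.0540)/0.8186 = 1.15. Fall = 0.2 × 1.15 = 0.23.
- Largest case, entry 10–19, μ = 6, σ = 6, r = 0.6: a = 0.667, b = 2.333. Bracket = 6 × (0.3194 − 0.0262)/0.2427 = 7.25. Fall = 0.4 × 7.25 = 2.9.

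Simulation over the whole grid agrees:

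| Registration score | Mean fall with no tool effect |
|---|---|
| 5–19 | 0.2 to 1.6 points |
| 10–19 | 0.7 to 2.9 points |

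**3. Chance that such a fall is significant.** For a non-tool fall d, SD of change s (assumed 4 to 5) and n users with both scores, a two-sided 5% paired test shows a significant fall with probability Φ(d√n/s − 1.96). Example: d = 1, s = 5, n = 100 gives Φ(2.00 − 1.96) = 0.52.

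| Non-tool fall | n = 50 | n = 100 | n = 200 |
|---|---|---|---|
| 0.5 | 0.11–0.14 | 0.17–0.24 | 0.29–0.42 |
| 1 | 0.29–0.42 | 0.52–0.71 | 0.81–0.94 |
| 2 | 0.81–0.94 | 0.98 or more | about 1 |

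A valid test of a tool effect would show a false improvement about 2.5% of the time. Natural recovery and concurrent care, where present, would add to the fall; neither is in these figures.

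**The case against.** The strongest reply is that the design is openly disclosed and ranked low. The missing control group is stated twice. The PHQ-9 in tool users comes last in the outcome section, after the primary, key secondary and survey outcomes. Outcomes collected only in intervention regions are called intermediate and partly exploratory, and PHQ-9 is not among the outcomes listed for the cost-effectiveness ratios. The limitations already caution about causal inference, and a condensed article may leave a component-level caveat to the full protocol.

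This stands as to weight and keeps the point at minor to moderate. It does not remove the point, because the objection is to a purpose stated in the text shown. Disclosing that there is no control group does not make an effect measurable, and no later analysis plan can recover a comparison that was not collected.

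The entry rule also tempers the size. Selection by clinical judgement rather than by a PHQ-9 cut-off, with severe cases excluded, limits regression to the mean without removing it. Concurrent care is an inference from primary care referral and guidance and from the lack of an exclusion; the article does not state it.

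A reader might infer that a significant fall is close to certain even for an inert tool. The documents do not support that: they give no variance, correlation or number of users, and under the assumed values a 1-point drift at 50 to 100 users is significant with probability 0.29 to 0.71. A reader might also infer that the result will be published as proof that Level 4 works. That would be a prediction about reporting, and the article states only the purpose.

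**Conclusion.** The point holds as one of wording and interpretation. The six-week PHQ-9 change is an uncontrolled change in people who enter while depressed, and it cannot measure the impact of the tool. That conclusion rests on the text alone. The figures rest on the assumed mean, SD, correlation and entry range: a fall of about 0.2 to 2.9 points from regression to the mean, which could well be significant depending on how many users return a six-week score. Severity is minor to moderate, because the outcome is intermediate and the trial's main comparisons are untouched.

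It may be tempting to treat a regression of six-week PHQ-9 on tool usage as the analysis that rescues the causal reading. It would not. Usage comes after registration and may reflect motivation, early improvement or contact with the guide. It would also need log data linked to individual scores, which neither Process evaluation nor Data management describes.

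**What to change.** 1. Outcome evaluation: replace "in order to measure the impact of the tool on depressive symptoms" with *to describe change in depressive symptoms among tool users; no effect will be attributed to the tool*.
2. Study aims and design: limit outcomes collected only in intervention regions to describing change, and remove the statement that they evaluate system-level impact.
3. Strengths and Limitations: add that the matched control regions do not cover the iFightDepression component, so recovery, regression to the mean and other care cannot be separated from a tool effect.
4. Results: report registration PHQ-9 separately for users with and without a six-week score, so that readers can judge how selective the follow-up is.

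The cost is three changes of wording and one descriptive table from scores already planned, with no new data collection. The downside is a weaker claim for the tool.

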### Process evaluation

The process evaluation will assess key aspects of implementation, such as reach, adoption, implementation, acceptability, and sustainability of the intervention. Multiple data sources will be used to capture these dimensions:

**Monitoring templates and trackers** to be completed by local research officers to document implementation activities (e.g., alliance functioning, awareness campaigns, training sessions, media engagement).**Semi-structured interviews** with local research officers to explore regional differences, facilitators, and barriers.**Satisfaction surveys for Level 1 and Level 3 trainees** to assess relevance, usability, and perceived impact of the trainings for professionals.**Satisfaction surveys for tool guides, and tool users** to assess relevance, usability, and perceived impact of the iFightDepression® tool.**Log data from the iFightDepression® tool** (e.g., number of registrations, repeat visits, total usage time) to evaluate engagement.**Focus group with stakeholders** in each country to evaluate the acceptability, implementation process, and sustainability of the intervention.

The design of the data collection instruments is grounded in three widely used implementation science frameworks. The Consolidated Framework for Implementation Research (CFIR) [20,78] guides the identification of barriers and facilitators across five domains (intervention characteristics, inner and outer settings, individual characteristics, and implementation processes) providing a nuanced understanding of contextual influences. The RE-AIM framework [21] informs the evaluation of key dimensions of implementation success, including reach, adoption, fidelity, and maintenance. Finally, the taxonomy of Proctor and colleagues [25] offers a structured set of implementation outcomes, such as acceptability, appropriateness, feasibility, and sustainability, that complement RE-AIM and enable a comprehensive assessment of how the intervention is integrated into practice. Together, these frameworks ensure that the process evaluation captures both contextual determinants and measurable indicators of implementation quality.

### Economic evaluation

The economic evaluation will use a cost-consequence analysis from both healthcare payer and societal perspectives. Costs considered include:

**Direct implementation costs** estimated using a micro-costing approach [79], which involves detailed tracking of resource use and unit costs.**Healthcare costs** related to suicide (attempts), based on published literature and/or hospital data.**Other societal or private costs** related to suicide (attempts), based on published literature and expert opinion (e.g., informal care).**Productivity losses**, calculated per full day of inpatient stay following a suicide attempt, its follow-up period or productivity loss due to premature mortality in case of a successful attempt.

Where feasible, country-specific cost estimates will be derived using local data sources. Outcomes linked to the cost estimates in incremental cost-effectiveness ratios include hospitalisations due to suicide attempts (primary economic outcome), deaths by suicide, and changes in public knowledge, attitudes, and mental wellbeing, as measured through the general population survey. Reporting will occur conform the CHEERS guidelines [80].

### Ethics

The study was conducted according to the guidelines of the Declaration of Helsinki. The trial will be carried out at all times in strict accordance with the principles of voluntariness, confidentiality and non-harm. Ethical approval was received in each participating country, from the Ethical Committee of the Ministry of Health, Albania (No. 6653, date. 10.09.2024), the Human Research Ethics Committee of the National Institute for Health Development in Estonia (Decision No. 1372, date 19.09.2024), the Ethics in research committee of the Psychology department of the University of York Europe Campus in Thessaloniki (No. 1078, dt 16.07.2024), the Social Research Ethics Committee (SREC) Log No: 2024−227 (date: 29.11.2024; population survey) and Log No: 2025−015 (date: 27/02/2025; trainings) in Ireland, and the Drug Research Ethical Committee (CEIm) of Hospital del Mar in Spain (2024/11534/I; date 06/11/2024). All participants, where data is collected, receive information about the study and provide informed consent before participating. For the evaluations of L1 and L3 training participants, and for patients using the online iFightDepression tool, informed consent was provided by clicking on the box in the electronic form. This format for informed consent was also used for all the general population survey participants in Greece and Albania, and for those responding to the survey online in Estonia, Albania, and Spain. For phone and face-to-face interviews, informed consent was provided verbally in these countries. Verbal consent was witnessed by the evaluator and recorded in the tool, and in Spain voice recordings were also taken of the informed consent. No data was collected from any minors during the course of this study.

### Data management

For this trial, data will be transferred and stored following the principles of the EC Directive on personal data protection and confidentiality, conform the General Data Protection Regulation (GDPR) (EC/2016/679). The general population survey data is anonymous, no personal details are collected, and the data will be collected by external, accredited, market research agencies. For the Level 1 and Level 3 trainings, pseudonymised data will be collected from participants through the LimeSurvey tool (https://www.limesurvey.org/), where the data from responses will be managed by KU Leuven. The patient data for the iFightDepression® tool will be stored securely on a secure server in Germany, and anonymised data will be provided to KU Leuven for analysis.

When processing and analysing the data, measures will be taken to eliminate the risk of identification of individual participants/people in the pseudonymised multi-country dataset, for example by collapsing country of origin categories when there is a small number of individuals in one specific country. Similarly, only aggregated anonymised data will be used in publications referring to the project.

Directive 2001/20/EC (Clinical Trials Directive), Regulation EU No 536/2014 (Clinical Trials Regulation), Regulation EU No 2017/745 (Medical Device Regulation) or Regulation EU No 2017/746 (In-Vitro Diagnostic Medical Devices Regulation) are not applicable to the project. No other additional regulatory documents are relevant for the project.

